### **Data collection**

Baseline patient characteristics will be obtained from standard patient-registry information at the HIU. This includes demographic information, comorbidities, and the findings at the time of angiography.

Outcomes will be assessed 3 and 12 months post-index angiogram through patient phone calls by a research coordinator associated with the HIU who will be trained expressly for this function. The research coordinator conducting the phone calls will not have access to the allocation list. The calls are made on behalf of the treating cardiologist at the HIU, and all patients will be encouraged to review cardio-protective meds with their family physician. The phone call follow-ups will ask patients to list their current, daily medications (and doses) without specific prompting in order to reduce bias. Attempts will be made to contact patients for a maximum of 30 days prior to being considered lost-to-follow-up. Reasons for loss-to-follow-up will be tracked.

For a sample of patients aged 65 and older, the Ontario Drug Benefit database will be used to examine the accuracy of the self-reported primary outcome and to further evaluate adherence using the medication possession ratio over the preceding year, which has been shown to be associated with both pill counts and clinical effects [47].

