## Objectives

The overarching goal of this project is to improve long-term use of secondary prevention medications for patients with CAD, and thereby reduce cardiovascular events through the use of an easily generalizable and sustainable intervention. The primary objective of this study is to assess if repeated mailing of an educational message and reminder to the family physician and the patient will decrease the proportion of patients who discontinue evidence-based secondary-prevention medications at twelve months post-STEMI. A secondary objective is to encourage cardiac patients and their primary care providers to discuss the benefits of long-term adherence to cardiac medications.

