### **Intervention**

The intervention was developed in concert with clinical experts from both primary care and cardiology, as well as experts in knowledge translation and medical decision-making. Personalized letters sent via post to the patient and their family physician at one, five, eight, and eleven months after their angiogram, signed by the interventional cardiologist (see Additional file 1: Appendix A for prototype). The letter for the family physician names the patient and provides brief evidence in support of long-term medication use for these patients. This was reviewed and edited with a series of family physicians from a different area of the province.

The patient letter provides a review of the importance and role of each of the cardiac medications and urges short- and long-term adherence (see Additional file 1: Appendix B for prototype). This educational aspect is designed to address knowledge and beliefs about medication use as a potential cause of poor adherence. The intervention explicitly encourages discussion of medication adherence with the family physician by asking patients to bring the letter to their family physician. It also asks patients to deliver the final page of their letter to their pharmacist; this page is written to the pharmacist urging them to participate in promoting long-term adherence. The intention is to facilitate recurrent discussions with primary care providers that emphasize long-term adherence and to address coordination of care and continuity of information as barriers to medication persistence. This letter was developed with iterative evaluations of understanding and acceptability amongst a series of cardiology patients at the HIU. The language in the patient letter is simplified to a grade six-level.

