### **Comparator/usual care**

Usual care in this context may include some contact between the admitting physician (generally not the interventional cardiologist) for the STEMI patient and the primary care provider (generally the family physician). This is usually in the form of a standard discharge summary mailed to the family physician’s office at the end of the hospitalization. The quality of such discharge summaries varies widely even within the same institution (and summaries frequently lack necessary information regarding medications) [41]. In keeping with the pragmatic nature of the trial, no attempt will be made to standardize the usual care arm [42].

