### **Outcomes**

The primary outcome is the proportion of living patients who describe taking all cardiac medication classes of interest measured at twelve months. This type of ‘all-or-none’ measure has been recommended for evaluating quality improvement interventions, especially related to medication utilization [43]. Specifically, we will assess whether patients are taking a statin, beta-blocker, angiotensin modifier (ACE or ARB), and aspirin at twelve months. All STEMI patients have reasonable evidence supporting these medications [3]; we anticipate that randomization will balance those patients for whom evidence is less clear or who might have contraindications to any of these medications.

We will also assess whether patients are taking these four medication classes plus a secondary antiplatelet (clopidogrel, prasugrel, or ticagrelor) at three months. Therefore, patients at three months will be dichotomized as to whether or not they are taking all five cardiac medication classes, and at twelve months they will be dichotomized according to whether they are taking all four relevant medication classes. The difference in the number of medication classes considered at three and twelve months relates to uncertainty in the evidence regarding the appropriateness of a secondary antiplatelet at this timeframe. Additional secondary outcomes include a comparison of: the proportion of patients who report actively taking each cardiac medication class of interest (item-by-item) at three and twelve months; the proportion of patients who report stopping medications due to side effects at three and twelve months; the proportion taking one or two or three medication classes concurrently at three and twelve months; and the proportion of patients with a perfect Morisky Medication Adherence Score (MMAS) for cardiac medication compliance at three and twelve months. The MMAS is a brief, standardized adherence questionnaire which excellent reliability [44], and has been shown to be predictive of cardiovascular medication adherence [45] and to be associated with control of blood pressure and cholesterol [44,46]. In addition, all patients will be asked at three months and twelve months whether they had a discussion with their family physician during past three months in which the provider had encouraged long-term cardiac medication compliance.

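### The 3-month outcome call gives control patients one component of the intervention, a prompt to review cardiac medicines with the family physician, nine months before the primary outcome

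*Protocol article*

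**What the plan says.** All passages are in the protocol article.

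- **Data collection.** "Outcomes will be assessed 3 and 12 months post-index angiogram through patient phone calls". At these calls "all patients will be encouraged to review cardio-protective meds with their family physician". No arm is exempt, and nothing limits the encouragement to the 12-month call. As to the sender, "The calls are made on behalf of the treating cardiologist at the HIU".
- **Intervention.** "The intervention explicitly encourages discussion of medication adherence with the family physician", by asking patients to take their letter to that physician. The letters are "signed by the interventional cardiologist". The closing summary of this section lists explicit instructions to discuss the matter with the family physician among the features that distinguish the intervention from usual care.
- **Objectives.** "A secondary objective is to encourage cardiac patients and their primary care providers to discuss the benefits of long-term adherence to cardiac medications".
- **Outcomes.** The primary outcome is taking all four medication classes at twelve months. At the 3-month and the 12-month call, patients are also asked "whether they had a discussion with their family physician during past three months in which the provider had encouraged long-term cardiac medication compliance".
- **Comparator/usual care.** Usual care is described as, usually, a discharge summary mailed to the family physician, and "no attempt will be made to standardize the usual care arm". A study call is not mentioned.
- **Sample size.** 50% in controls, an 11-point increase, variance inflation 1.02, 80% power, 652 analysed, 815 randomized. No allowance is made for the call.
- **Limitations.** Carry-over through pharmacists and accidental unblinding of the caller are discussed. The encouragement in the call is not.

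**The concern.** The trial tests whether contact on a cardiologist's behalf, including a prompt to talk to the family physician, keeps patients on their medicines. From month 3 the trial itself gives a spoken form of that prompt to every control patient it reaches. The Allocation section clusters by family physician expressly to prevent contamination, yet this route to the controls is left open.

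The timing is sensitive on the protocol's own reasoning. Use of all four classes falls from 78% at discharge to 63% by 90 days (Participants and Setting). Pharmacists commonly dispense no more than three months' supply, and the letters were timed to precede renewals (Intervention). A 3-month call therefore reaches controls near a likely renewal. It may add less in the intervention arm, which by then has had the one-month letter and the two-month postcard.

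What is at stake is the size of the 12-month contrast and what it describes. If controls respond to the prompt, the estimate compares the mailings with usual care plus a prompting call, not with the usual care that would be met in a roll-out. Analysis cannot undo this, because every contacted control is exposed.

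**Working it through.** **1. Does the prompt match an intervention component?**

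| Feature | Intervention arm | Control arm, through the call |
|---|---|---|
| Prompt to discuss medicines with the family physician | Yes, in the patient letters | Yes, spoken at 3 months |
| On behalf of a cardiologist | Interventional cardiologist | Treating cardiologist |
| Letters to the patient at 1, 5, 8 and 11 months | Yes | No |
| Letters to the physician with evidence summary | Yes | No |
| Pharmacist page, two-month postcard | Yes | No |

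One component is shared; the rest is not.

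**2. Which outcomes can the 3-month prompt reach?**

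- Primary outcome at 12 months: yes, 12 − 3 = 9 months later.
- 3-month outcomes: no. They are collected in the same call and describe the time before it.
- 12-month discussion item: indirectly at most. It covers the past three months, about months 9 to 12, so its window opens about 9 − 3 = 6 months after the prompt.

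**3. Reproducing the planned sample size.** Inputs from Sample size: p1 = 0.50, p2 = 0.61, 5% level (taken as two-sided), 80% power, variance inflation 1.02, 80% participation. With p̄ = (p1 + p2)/2 = 0.555,

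n per arm = [1.960·√(2p̄(1−p̄)) + 0.842·√(p1(1−p1) + p2(1−p2))]² / (p2−p1)²

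= [1.960 × 0.7028 + 0.842 × 0.6985]² / 0.0121 = 319.2, rounded up to 320.

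Total: 2 × 320 × 1.02 = 652.8, or 2 × 319.2 × 1.02 = 651.2 without rounding first; the plan states 652. Randomized: 652/0.80 = 815, as stated. The plan's figures reproduce, and at 652 there is no reserve above 80% power.

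**4. Sensitivity of power to a control lift.** The document does not give the effect of the call, so lifts of 1 to 4 points are an assumption. The effective number per arm is 652/(2 × 1.02) = 319.6, and

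power = Φ{ [(p2−p1)·√319.6 − 1.960·√(2p̄(1−p̄))] / √(p1(1−p1) + p2(1−p2)) }.

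Example with controls at 52% and intervention at 61%: (0.09 × 17.878 − 1.960 × 0.7011)/0.6982 = 0.336, so power is 63%.

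| Control lift (points) | Intervention gains nothing | Intervention gains half as much | Both gain equally |
|---|---|---|---|
| 0 | 80% | 80% | 80% |
| 1 | 72% | 76% | 80% |
| 2 | 63% | 72% | 80% |
| 3 | 53% | 68% | 81% |
| 4 | 43% | 64% | 81% |

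In the first scenario the contrast falls from 11 to 10, 9, 8 or 7 points; in the second to 10.5, 10, 9.5 or 9; in the third it stays at 11.

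**5. Better follow-up than planned.** Sample size reports participation above 90% in similar studies. At 90%, 815 × 0.90 ≈ 734 are analysed and starting power is about 84%. With no gain in the intervention arm, lifts of 1 to 4 points then give 77%, 68%, 58% and 48%.

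**The case against.** The strongest reply is that one spoken prompt is small beside the full package. Controls get no written evidence, no repeated letters, no physician letter, no pharmacist page and no postcard. This stands: it is wrong to say that controls receive the intervention, or its active message as a whole.

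Several stronger readings are tempting, and the document does not support them:

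- **Same sender.** The letters come from the interventional cardiologist and the calls are made for the treating cardiologist. The two may be the same person, but the protocol does not say so.
- **A promise of untouched usual care.** The comparator section allows usual care to vary and declines to standardize it. It makes no such promise. What remains is that a uniform prompt added by the trial is not ordinary variation in care and is not described as part of the comparator.
- **Damage to the discussion outcome.** The 3-month answer precedes the prompt, and the 12-month window opens about six months after it.
- **An uninterpretable null result.** The expected direction is towards the null, so a positive result would not be put in doubt. A null result need not be explained by a single prompt, though dilution could not be ruled out.

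It is also fair to say that the prompt goes to both arms, so holding the intervention arm at 61% is the worst case, and that higher participation would give some reserve. Both points are shown in the working. They soften the range but do not remove the problem, because nothing in the protocol establishes that both arms would gain equally.

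**Conclusion.** The concern holds for the primary 12-month comparison. The protocol names prompting a discussion with the family physician as a distinguishing part of the intervention, and then gives that prompt to controls at 3 months. The usual-care description, sample size and limitations do not take account of it.

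The likely effect is dilution of the primary contrast, not bias in favour of the intervention. Its size is unknown. The power range runs from no loss (equal gain in both arms) to 43% (a 4-point control lift with no gain in the intervention arm). It rests on assumed lifts and on the plan's own 50%, 61%, 1.02 and 652, and it shows sensitivity, not an expected loss. Severity is moderate: the direction is conservative and only one component is shared, but the dilution is avoidable and cannot be repaired at analysis.

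**What to change.** Make the 3-month call script measurement-only. Give the general encouragement at the close of the 12-month call, after all outcomes are recorded. The end-of-trial note to family physicians, agreed with the ethics board, is unaffected.

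The cost is a script change and the ethics board's agreement. Consent is taken verbally at outcome assessment, and the protocol does not say whether the board relied on this encouragement, so agreement should be sought and not presumed. The small downside is that patients in both arms do not get a general prompt at 3 months. The change concerns only the routine encouragement to all patients; how a caller handles a particular problem that a patient reports is a clinical matter outside this point.

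If the prompt must stay at 3 months, describe the comparator as usual care plus a prompting outcome call, and add the possible dilution of the 12-month contrast to the limitations. That costs only wording, but the dilution remains.

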### **Ethical considerations**

Research Ethics Board (REB) approval was received at Hamilton Health Sciences Centre and McMaster University (project number 11–191). Given the low risk nature of the intervention, which falls within the realm of continuity-of-care and circle-of-care, the REB agreed that verbal consent at the time of outcome assessment is the most appropriate design to test this pragmatic intervention. Thus, there is no formal recruitment process; as mentioned above, all eligible patients within the registry at the HIU are allocated to intervention or control one-week post-STEMI. To gain REB approval, we agreed to provide a note to the family physician of all included patients describing the patient-reported outcomes (*e.g.*, current medications and adherence) at the end of the trial.

### **Data management**

All patient data will be collected directly into a password-protected database and will not be removed from the server at the HIU research office. Necessary information for contacting the participants (*e.g.*, name, phone number) will be kept in a separate, password-protected file from the study data, which will have no patient identifiers. The outcome data (without any identifiers) will be transferred from the database into a statistical package for analysis.

### **Analysis**

Descriptive statistics will be calculated for all variables of interest: continuous variables with a normal distribution will be summarized using means and standard deviations (medians and inter-quartile ranges in the case of skewed distributions), whereas categorical variables will be summarized using frequencies and proportions.

We hypothesize that the intervention will result in a greater proportion of patients who report taking each cardiovascular medication class of interest at 12 months post-angiography. The absolute difference in proportions will be calculated for all primary and secondary dichotomous outcomes, together with 95% confidence intervals adjusting for clustering by family physician [48]. The statistical significance of differences between arms will be evaluated using chi-squared tests, adjusted for clustering by family physician.

Exploratory multivariable analyses will be carried out using generalized estimating equations (GEE) to identify potential baseline predictors of adherence. Potential effect modification by treatment—medical management versus coronary artery bypass graft (CABG) versus angioplasty—and attendance at cardiac rehabilitation will be explored by including interactions between these two variables and group. It is plausible that this analysis will suggest a need for tailored interventions for these subgroups. A further exploratory analysis will be conducted focusing on patients who reported taking all five cardiac medication classes and had perfect MMAS scores at three months using a multivariable model to examine covariates predicting late-onset discontinuation. In addition, a planned sensitivity analysis will exclude those patients who did not have a family physician, as we would expect such patients to be more likely to discontinue their cardiac medications.

Analyses will be performed on an intention-to-treat basis. No interim analyses are planned. All analyses will be carried out using the SAS Version 9.2 statistical program (SAS Institute, Cary, NC, USA).

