### **Participants and Setting**

In Ontario, healthcare is financed through a single-payer (publicly administered) system. There are no co-payments for visits to generalist or specialist physicians or for care provided in hospitals for patients of any age, and almost all licensed prescription medications are covered for patients 65 and over. Patients younger than 65 years pay for medications out-of-pocket or through private insurance plans, or are covered by the provincial plan if they qualify for social support.

In this study, eligible patients are adult patients (>18 years) with a diagnosis of STEMI, who undergo a coronary angiography procedure (with or without angioplasty), at the Heart Investigation Unit (HIU) in Hamilton, Ontario, and who are alive at hospital discharge. In keeping with the pragmatic approach to study design, no other exclusion criteria will be applied. The HIU is the only catheterization lab in its region, with a catchment population of almost 1.5 million people. More than 700 STEMI patients undergo an angiogram there each year. Studies at the HIU have highlighted excellent rates of prescribing of evidence-based therapies at discharge post-STEMI, but substantial reduction in use starting three months following discharge [39,40]. While 78% of STEMI patients leave the HIU taking a statin, an ACE-inhibitor (or ARB), a beta-blocker, and aspirin, by 90 days the proportion still taking all four of these medication classes falls to 63% (unpublished data from the Strategic Management of Acute Reperfusion and Therapies in Acute Myocadial Infarction (SMART-AMI) study).

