### **Allocation**

The randomization schedule was computer-generated by a statistician independent of the study, using a permuted block design with randomly varying block lengths of four, six, or eight. Eligible patients are randomly allocated to one of the two treatment arms. Although enrolment of more than one patient treated by a particular family physician is expected to occur infrequently, randomization will be carried out to ensure that, once a patient from any family physician is randomized, all future patients seen by that family physician will automatically be assigned to the same arm. This is necessary to avoid contamination (with one family physician having patients in different intervention arms). Roughly one-half of patients will be allocated to each study arm (the actual allocation ratio will depend on the size of the clusters). Based on pilot data, we anticipate that approximately 10% to 15% of patients will not have a family physician. In keeping with the pragmatic design of the trial, a patient without a family physician will be included (receiving only the patient-level intervention).

Randomization is delayed by one week (after the angiogram) to permit time to identify and exclude patients with in-hospital death. Randomization will continue until the target sample size is achieved. The anticipated duration of enrolment is 15 months. The allocation sequence will be concealed from the investigators and outcome assessors; only the study coordinator who will be sending out the letters will have access to the un-blinded allocation list.

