### **Sample size**

The sample size for this design is based on the following assumptions: an assumed absolute increase in the proportion of patients taking all four cardiovascular medication classes of 11% at twelve months post-STEMI; an estimated control group proportion of 50%, and a variance inflation factor of 1.02 (derived from an intra-cluster correlation coefficient of 0.019 calculated from data in the SMART-AMI registry and assuming an average cluster size of 1.2 based on pilot data). To achieve 80% power to detect a significant main effect of the intervention using a Chi-squared test at the 5% level of significance, 652 patients would be required. We will randomize 815 patients to account for an estimated participation rate of 80% at the 12-month follow-up. This dropout rate is conservative based on similar studies at the HIU where the participation rate has been greater than 90% over even longer time periods [40].

The expected effect size is slightly higher than the effect seen in the previous Canadian trial to account for the fact that the intervention is multifaceted (directed at both physician and patient) and occurring later post-STEMI (reducing the expected control group rate and therefore the possibility of a ceiling effect). Based on this sample size calculation, and the rate of STEMI patients presenting to the HIU, we anticipate that it will take approximately 15 months to complete the recruitment for this study.

We will use a kappa statistic to assess agreement between the self-report of the primary outcome and the corresponding objective data from the Ontario Drug Benefit database. Based on an anticipated overall proportion of 56% at 12 months (average of intervention and control arm) and an anticipated kappa of 0.88, we would consider acceptable agreement if the lower limit of the 95% confidence interval around kappa does not drop below 0.80. Therefore we will evaluate validity of the primary outcome in a random selection of 138 patients aged 65 or greater.

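### The primary comparison adjusts only for clustering and uses no baseline covariate; pre-specifying adjustment for family-physician status and age would give a modest gain in precision at little cost

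*Protocol article*

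**What the plan says.** The Analysis section sets the effect measure and the test. "The absolute difference in proportions will be calculated for all primary and secondary dichotomous outcomes", with 95% confidence intervals that allow for clustering, and then: "The statistical significance of differences between arms will be evaluated using chi-squared tests, adjusted for clustering by family physician". The Sample size section is built on the same chi-squared test.

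Baseline variables appear elsewhere in the Analysis section, but not in the primary comparison:

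- Exploratory GEE models are to look for possible baseline predictors of adherence.
- Index treatment and cardiac rehabilitation are explored as possible effect modifiers.
- A sensitivity analysis leaves out patients without a family physician, because "we would expect such patients to be more likely to discontinue their cardiac medications".

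Under Allocation the plan anticipates that "approximately 10% to 15% of patients will not have a family physician". Such patients are randomised and receive only the patient-level part of the intervention. Allocation uses permuted blocks with no stated stratification, and later patients of a family physician take the arm of the first.

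Participants and Setting says that almost all prescription drugs are covered from age 65, whereas "Patients younger than 65 years pay for medications out-of-pocket or through private insurance plans", unless they qualify for provincial cover through social support. Data collection takes demographics, comorbidities and angiography findings from the unit's registry.

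**The concern.** The plan gives its own reason to think that one baseline factor, having no family physician, is related to the outcome. It also describes a coverage rule that makes age a plausible second factor, and its Background lists finances among patient-level reasons for non-adherence. The first factor must be known in order to allocate, and the second should be in the registry demographics. The primary comparison uses neither, and allocation is not described as stratified by them.

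When a baseline factor predicts the outcome, adjusting for it narrows the confidence interval of the risk difference and removes the part of the estimate that is due to chance imbalance in that factor. The sensitivity analysis does not do this, because it changes the population by dropping patients.

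A few points of power could be useful here. The Background reports absolute gains of 9% to 10% in two earlier statin reminder trials, below the 11 points on which this trial is sized.

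**Working it through.** **Inputs from the Sample size section.** Control proportion 50%; "an assumed absolute increase in the proportion of patients taking all four cardiovascular medication classes of 11% at twelve months post-STEMI", so 61% in the intervention arm; "a variance inflation factor of 1.02"; 80% power; 5% significance level, taken as two-sided because that reproduces the stated total; 80% participation at 12 months.

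**1. The plan's own figure.** With mean proportion 0.555, the patients needed per arm are

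n = [1.96·√(2·0.555·0.445) + 0.842·√(0.50·0.50 + 0.61·0.39)]² / 0.11² ≈ 319.2, rounded up to 320.

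The total is 640, and 640 × 1.02 = 652.8, against the stated 652. Then 652 / 0.80 = 815. Both figures reproduce. Power at 652 with inflation 1.02 is 80.05%. (The stated intra-cluster correlation and cluster size give 1 + 0.2 × 0.019 = 1.0038 and not 1.02. The stated value is the more conservative and is used here; with 1.0038 power would be 80.7%.)

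**2. Gain from family-physician status.** The share of outcome variance explained by a yes/no factor with prevalence q and outcome gap d is

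R² = q(1 − q)d² / (0.555 × 0.445).

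Adjustment multiplies the variance by about (1 − R²), so the effective number per arm becomes 652 / (1.02 × 2 × (1 − R²)). Prevalence is the plan's 10% to 15%. **The gap is assumed**, since the documents give none.

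| Assumed gap (points) | R², q = 10% | Power | R², q = 15% | Power |
|---|---|---|---|---|
| 10 | 0.36% | 80.19% | 0.52% | 80.25% |
| 20 | 1.46% | 80.62% | 2.06% | 80.86% |
| 30 | 3.28% | 81.34% | 4.65% | 81.89% |
| 40 | 5.83% | 82.36% | 8.26% | 83.33% |

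The gain runs from 80.19 − 80.05 = 0.14 points to 83.33 − 80.05 = 3.28 points. The equivalent sample size for unchanged power runs from 650 down to 598, instead of 652.

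**3. Gain from age.** Assume that 40% to 50% are aged 65 or over and that the gap is 5 to 20 points. Then R² is 0.2% to 4% and power is 80.1% to 81.7%.

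**4. Several factors together.** The totals below are assumptions.

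| Total R² | Power | Equivalent N | 95% CI half-width (points) |
|---|---|---|---|
| 0 | 80.0% | 652 | 7.7 |
| 5% | 82.0% | 619 | 7.5 |
| 10% | 84.0% | 587 | 7.3 |

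If the true effect were 10 or 9 points, power with the planned test would be about 72% or 63%. With total R² of 5% to 10% it would be about 74% to 76%, or 65% to 67%.

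**5. Check by simulation.** The setting was 640 patients, 6,000 runs, a linear risk model with robust standard errors, clustering ignored, and 12.5% without a family physician. With a 20-point gap, power was 80.4% unadjusted and 81.2% adjusted. With age added (50% aged 65 or over, 10-point gap), it was 80.1% and 81.0%. Type I error was near 5% with and without adjustment.

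**6. Size of chance imbalance.** With 326 analysed per arm, the standard deviation of the between-arm difference in the share without a family physician is √(0.125 × 0.875 × 2/326 × 1.02) = 0.026. In 95% of trials this shifts the risk difference by no more than 1.96 × 0.026 × 0.20 ≈ 1.0 point for a 20-point gap, and about 2.1 points for a 40-point gap.

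**The case against.** The case for leaving the analysis alone is substantial, and most of it stands.

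- **The planned test is sound.** It carries the adjustment that the cluster design requires, it is valid under randomisation, and it is the test on which the trial was sized. A reader might infer that the test is simply unadjusted, or that the trial is underpowered because of it. The documents do not support either.
- **No predictor is called strong.** A reader might infer that the plan identifies strong predictors and then ignores them. In fact predictors are still to be looked for. Only lack of a family physician has a stated direction, the age-65 rule is a description of drug coverage, and index treatment is named only as a possible effect modifier. Nothing says that surgery or final medical management is settled by one week, when allocation takes place.
- **No patients are lost by the planned analysis on this account.** Those without a family physician are in the intention-to-treat comparison; only the sensitivity analysis drops them. Covariate adjustment adds nobody.
- **Imbalance is a minor matter.** The likely shift of 1 to 2 points is already covered by an interval of ±7.7 points, and with an average cluster size of 1.2 the inherited allocation changes little.
- **Covariate detail may sit in an analysis plan that is not shown.** That is possible. However, the article does state its primary method, so the point concerns a stated choice and not an omission.

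These objections reduce the point to its proper size but do not remove it. The information is already collected or needed for allocation, the target stays an absolute difference in proportions, and type I error is unaffected.

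**Conclusion.** The point holds as a modest efficiency improvement. The primary comparison is valid and delivers its planned 80% power, but it leaves unused a baseline factor that the plan itself expects to matter, and also age.

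On the plan's prevalence of 10% to 15% and an assumed gap of 10 to 40 points, family-physician status alone is worth about 0.1 to 3.3 points of power. Reaching 82% to 84% depends on a total R² of 5% to 10%, for which the documents give no evidence. Larger gains would need a stronger predictor. Use of all four drug classes at discharge (78% in the unit's earlier data) might be one, but it is not listed among the baseline data.

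**What to change.** Before unblinding, pre-specify as the primary analysis a covariate-adjusted absolute risk difference at 12 months. One way is a GEE model clustered by family physician, followed by standardisation over the analysed patients, with a standard error that respects the clusters. Adjust for family physician yes/no and for age, stating how age is coded and whether the change at 65 is included. Add index treatment only if it is recorded before randomisation. Leave out rehabilitation attendance, which arises after allocation. State how missing covariates are handled and how patients without a family physician enter the clustering, for example each as a cluster of one.

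Keep the cluster-adjusted chi-squared test and its risk difference as a supporting analysis, and keep the sensitivity analysis that excludes patients without a family physician.

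The cost is a few lines of text and slightly more analysis work, with no new data and no change to the sample size. If an identity-link model is chosen instead of standardisation, name a fallback in case it does not converge.
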